#### Economic evaluation

**Base-case analysis.** Using a micro-costing and bottom-up approach, total costs will be approximated from a societal perspective in the GST arm and the continued CBT-E arm, in line with recent best practices [52]. Essentially, each element of service use will be multiplied by an appropriate unit cost in euros. If necessary, unit costs will be updated, using the 2023 consumer price index [55]. Relevant unit costs for each type of service are outlined in contemporary Dutch costing manuals for healthcare services [56, 57]. Intervention costs, healthcare costs, patient and family costs and productivity losses for unpaid work, paid work and education will be estimated. Productivity losses will be quantified, using a friction cost approach that is confined to the time period required to replace one sick employee. In case of major uncertainty surrounding the abovementioned analyses, cost estimates will be founded on the most conservative assumptions.

Primarily, economic evaluations aim to compare the additional costs and outcomes of GST to those of CBT-E. In the economic evaluation of the current protocol, collected data will be used to conduct a cost-effectiveness analysis (CEA) and a cost-utility analysis (CUA). On the one hand, a CEA expresses all clinical treatment effects of GST and CBT-E relative to their economic costs, using the incremental cost-effectiveness ratio (ICER). On the other hand, a CUA aims to compare all gains in quality adjusted life years (QALYs) of GST and CBT-E to their respective economic costs, using the incremental cost-utility ratio (ICUR).

In short, the ICER is aimed at dividing the difference in treatment effects of GST and CBT-E by the difference in total costs of both treatments. For instance, the total difference in clinical EDE-Q gains of both GST and CBT-E can be weighed against the cost differences of both treatments. Using a similar incremental cost-utility ratio (ICUR), the difference in QALY gains of both treatments is divided by their respective cost differences. QALYs are computed based on the measured EQ-5D-5 L data, using converted EuroQol utility scores [58].

In order to verify the robustness of the obtained ICER and ICUR, non-parametric bootstrapping techniques will be conducted. These bootstrap replications are characterized by random sampling based on individual input data, yielding information about the magnitude and distribution of most pairwise cost-effect estimates. In order to facilitate this objective, the bootstrap replications will yield the 95% confidence intervals for the obtained ICER and ICUR within a cost-effectiveness plane, surrounding the 2.5th and 97,5th percentiles [29]. While the horizontal axis of a cost-effectiveness plane depicts the difference in effectiveness between two treatments, the vertical axis represents the cost difference between two treatments [59].

Subsequently, a cost-effectiveness acceptability curve will be plotted in order to determine the maximum amount of money that society is willing to pay for one unit of clinical improvement or one unit of QALY gains. This maximum amount of money is also called the willingness-to-pay (WTP) ceiling ratio [29]. In the Dutch healthcare system, ceiling ratios of € 20,000, € 50,000 and € 80,000 per QALY exist, depending the disease burden that will be determined based on the study population [60]. If the computed ICER or ICUR for a certain treatment is likely to fall below these thresholds, that treatment is usually considered cost-effective. In order to determine whether GST is cost-effective over CBT-E in the Netherlands, the cost-effectiveness acceptability curve will display the probability that the ICER and ICUR of GST fall below a range of existing ceiling ratios. This computed probability is based on the obtained bootstrap replications for the ICERs and ICURs of GST. Lastly, multivariate sensitivity analyses will be conducted to examine whether different assumptions regarding cost prices and volumes may affect the obtained ICERs and ICURs.

**Budget impact analysis.** Subsequent to these base-case analyses, a budget impact analysis (BIA) will be conducted according to existing quality guidelines [61, 62]. In short, this BIA aims to inform Dutch healthcare stakeholders on the foreseeable financial consequences of implementing GST on a regional or national level. Importantly, the BIA will be tailored to the relevant cost categories for separate stakeholders. Appropriate assumptions regarding data distribution of cost components will be developed in order to objectively quantify the budget impact of GST for a variety of stakeholders over a 3-year time horizon. In order to do so, the BIA will target at least four parameters: (1) the national prevalence of the eligible GST intervention population in The Netherlands, (2) the expected GST implementation rate in clinical practice, (3) average GST trajectory costs, and (4) average CBT-E trajectory costs. All four parameters mentioned above will be subjected to univariate and multivariate sensitivity analyses in order to estimate the robustness of the national GST budget impact in different scenarios. Lastly, the BIA will be conducted from a societal, healthcare and commercial payer perspective.

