### Study population

Patients are eligible for participation in the current trial, if they meet the following inclusion criteria: (1) an age of 16 years or older; (2) the ability to read and speak the Dutch language; (3) a DSM-5 classification of anorexia nervosa (AN), bulimia nervosa (BN), or other specified feeding and eating disorder (OSFED) that identifies as an atypical AN or BN variant with a low frequency or limited duration of binges / purges and (4) failure to show an early response after 8 sessions CBT-E. The Jacobson-Truax Reliable Change Index (RCI) approach will be used to assess whether the early CBT-E response is significant or not [35]. Exclusion criteria include: (5) the presence of an acute psychosis; (6) a clinically diagnosed autism spectrum disorder (ASD); (7) currently receiving schema therapy elsewhere and (8) an IQ below 80.

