### Treatments

#### Intervention: Group Schema therapy (GST)

GST will consist of 26 weekly 90-minute group sessions, tailored to people with an ED. If necessary, GST can be supplemented with 8 individual sessions used for facilitating the GST process. The individual sessions can for example be used for imagery rescripting of adverse childhood experiences. Subsequent to randomization, patients may have to wait for at most three months before initiating their GST treatment in mental healthcare, as it is a half-open group, with an entry and exit moment every 13 weeks. During this waiting period, 5 individual treatment sessions will take place that focus on explaining the ST model, placing the ED symptoms and behaviors in the context of coping modes, and organizing these in a mode map conceptualization. This is an important foundation for the upcoming GST. The following sessions focus on recognizing and changing personal coping modes regarding eating disorder symptoms and underlying early maladaptive schemas. These sessions are also aimed at developing and strengthening the healthy adult mode. In doing so, GST combines interpersonal, experiential, cognitive and behavioral elements in a unified ST approach. On top of that, a psycho-education webinar will be organized for relatives.

**Theoretical framework for GST: a group format of ST.** In short, ST provides an integrative approach that is fundamentally geared towards treating people with deeply entrenched self-identity difficulties and interpersonal problems, which are reflected through maladaptive schemas and schema modes [15]. In clinical practice, ST was deemed effective for treating personality disorders [16], including ST in a group setting [18]. On the one hand, maladaptive schemas refer to a pervasive pattern of beliefs regarding oneself and one’s relationship with others consisting of one’s memories, emotions, cognitions and bodily sensations. On the other hand, schema modes are characterized by one’s moment-to-moment thoughts, feelings and behaviors when maladaptive schemas interact with coping mechanisms [23].

In terms of treatment delivery, ST emphasizes experiences, while CBT-E mainly emphasizes cognitions and behavior. In GST, the connection between participants in the group format is considered an amplifier for the effects of ST. On top of that, GST ensures a healthy therapeutic relationship to provide corrective experiences in favor of the patient’s needs during treatment [23].

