#### Economic evaluations

Societal costs will be determined using the Treatment Inventory of Costs in Patients with psychiatric disorders questionnaire (TIC-P). This validated instrument assesses costs by measuring consumed healthcare resources and productivity losses [51]. Lastly, the economic evaluation study will be performed in line with the Dutch Guidelines of the National Health Care Institute [52].

During the entire data collection phase, the TIC-P and the aforementioned clinical instruments will be mostly measured on the same time points (T0-T3). See Table 1.

**Table 1 Tab1:** all questionnaires for each measurement point in time

Instruments	Time points^a^					
	Pre-measure	Post-measure	T0	T1	T2	T3
Demographic and clinical characteristics	x					
EDE-Q	x	x		x	x	x
TIC-P			x	x	x	x
EQ-5D-5 L			x	x	x	x
EDQOL			x	x	x	x
SMI-ED			x	x	x	x
YSQ-S3	x			x	x	x
CTQ-SF	x					
BSI			x	x	x	x
CPQ	x					
BMI	x		x	x	x	x

^a^ Pre-measure: measurement before the initial session of CBT-E, post-measure: measurement after 8 sessions of CBT-E, T0: baseline measurement, T1: measurement following the end of treatment, T2: measurement at 6-month follow-up, T3: measurement at 12-month follow-up

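### As worded, the friction-cost limit covers unpaid work and education as well as paid work, although its rationale holds for paid work only

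*Protocol article*

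**What the plan says.** The rule stands in the protocol article under Data analysis, Economic evaluation (Base-case analysis). The perspective is set first: "total costs will be approximated from a societal perspective in the GST arm and the continued CBT-E arm". The cost categories follow, among them "patient and family costs and productivity losses for unpaid work, paid work and education will be estimated". The very next sentence gives the valuation method: "Productivity losses will be quantified, using a friction cost approach that is confined to the time period required to replace one sick employee".

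The article states no other valuation method for unpaid work or education. The section on data collection (Economic evaluations) says of the TIC-P, "This validated instrument assesses costs by measuring consumed healthcare resources and productivity losses", and Table 1 schedules it at T0, T1, T2 and T3. The same section adds that "the economic evaluation study will be performed in line with the Dutch Guidelines of the National Health Care Institute". Eligibility starts at "an age of 16 years or older".

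The sensitivity analyses at the end of the economic section vary the prices and volumes of cost items. They name neither the valuation method nor the friction period.

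**The concern.** A friction-cost approach rests on replacement. Once the employer has filled the post, production is taken to be restored and the loss to society ends. That reasoning needs an employer and a vacancy. A student who misses school, or someone who cannot run a household or care for a relative, is not replaced in this way, so the loss continues for as long as the absence does.

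The article uses the same term in two consecutive sentences. The first spreads it over three categories, and the second puts a time limit on it without exception. An analyst who follows the text would stop counting unpaid work and education after the friction period.

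Total societal cost enters the ICER, the ICUR and the acceptability curve, and so bears on the hypothesis that GST is more cost-effective. With entry from age 16, some participants can be expected to be in education, though the article does not say how many. Two consequences are possible: costs in these categories are too low in both arms, and a real difference in return to education or household tasks reaches the incremental cost only in part.

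**Working it through.** The article states no figure for this rule, so there is nothing to reproduce. The check has two parts: what the text covers, and what a limit of this kind does to a cost difference.

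**Scope of the rule**

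| Category listed | Valuation stated | Is anyone replaced by an employer? |
|---|---|---|
| Paid work | friction cost, limited to replacement time | yes |
| Unpaid work | the same sentence, no exception | no |
| Education | the same sentence, no exception | no |

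**Inputs from the article**
- Length of GST: 26 weeks ("GST will consist of 26 weekly 90-minute group sessions").
- Wait before GST: up to three months, about 13 weeks.
- Last follow-up: 12 months after the end of treatment, 52 weeks.
- Observation window in the GST arm: 26 + 52 = 78 weeks without a wait, and up to 13 + 26 + 52 = 91 weeks with the longest wait. The window is long enough for a limit to bind.

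**Assumed, because the article does not give them:** the friction period F and the absence lengths.

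**Step 1. Share of one continuous absence of L weeks that is counted: min(F, L) / L**

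| L (weeks) | F = 10 | F = 25 |
|---|---|---|
| 26 | 10/26 = 38% | 25/26 = 96% |
| 39 | 10/39 = 26% | 25/39 = 64% |
| 91 | 10/91 = 11% | 25/91 = 27% |

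**Step 2. Arm difference with fixed absences: min(F, b) − min(F, a)**
- a = 30, b = 40: the true difference is 10 weeks. The counted difference is 0 for every F from 8 to 26, because both absences outlast the limit.
- a = 10, b = 20: the true difference is again 10 weeks. The counted difference is 0 at F = 8, then 2 at F = 12, 6 at F = 16, and the full 10 at F = 20 or more.

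The first pair gives zero by construction. It shows that a difference can be lost, not that this is likely.

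**Step 3. Arm difference with varying absences.** Take exponential durations with mean m. The mean counted up to a limit c is m × (1 − exp(−c/m)). Without the friction limit, c is the 91-week window.

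Means of 20 and 30 weeks:
- Without the limit: 30 × (1 − exp(−91/30)) − 20 × (1 − exp(−91/20)) = 8.77 weeks.
- F = 8: 30 × (1 − exp(−8/30)) − 20 × (1 − exp(−8/20)) = 0.43 weeks, 5% kept.
- F = 12: 0.87 weeks, 10% kept.
- F = 26: 2.84 weeks, 32% kept.

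Means of 5 and 8 weeks:
- Without the limit: 3.00 weeks.
- F = 8: 1.07 weeks, 36% kept.
- F = 12: 1.67 weeks, 56% kept.
- F = 26: 2.72 weeks, 91% kept.

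The effect therefore depends on absence length relative to F, and the article fixes neither.

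**The case against.** The strongest reply is that the sentence limits itself. A period defined by replacing an employee applies naturally to people who have a job, so the authors may have meant paid work only. The article also calls its analysis section a general plan and ties the economic evaluation to national guidelines and costing manuals, which may value the three categories separately. On this view the fault is loose wording in a condensed paper.

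Part of this stands. Intent cannot be settled from the article, and a wording slip is quite possible. But the limit is attached to a term that the sentence before has just defined to include unpaid work and education. The guideline references are general, and no passage exempts the two categories or values them in another way. This is a stated rule that does not fit two of the three things it covers, rather than detail left for later. The provision for conservative assumptions applies only under major uncertainty and does not lift the limit. Lost time could be regarded as a volume in the sensitivity analyses, but those analyses do not mention the limit.

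The reply is also right about size. The absence lengths above are assumptions, and nothing in the article says that patients miss school or household tasks for months on end. If the limit is applied separately within short recall windows, it may hardly bind.

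A reader might infer from the long-absence examples that real arm differences will disappear from the ICER and ICUR. The documents do not support that. They show that a difference could shrink, and in the extreme be lost, under a literal application.

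**Conclusion.** The point holds as a fault in the stated rule. As worded, the friction-cost limit reaches unpaid work and education, where it has no rationale and conflicts with the societal perspective. Applied literally, it would understate these costs whenever an absence outlasts the friction period, and could shrink the arm difference for such absences.

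The size cannot be determined from the article, which gives no friction period, TIC-P recall window, absence lengths or share of participants in education. The illustrations run from 5% of a difference kept (means of 20 versus 30 weeks, F = 8) to 91% kept (means of 5 versus 8 weeks, F = 26). They rest on an assumed F of 8 to 26 weeks and assumed exponential durations. If absences are short, the effect may be small.

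Only the societal cost results are concerned. The EDE-Q comparison is unaffected. The sentence should be corrected before the cost data are analysed, so that the choice is not made after the results are known.

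**What to change.** In the base-case paragraph, restrict the rule to paid work and state a separate rule for the other two categories. Suggested wording: *The friction cost approach applies to productivity losses from paid work only. Losses in unpaid work and education are valued as the reported time lost, with the same recall or extrapolation handling as other TIC-P volumes, multiplied by the applicable unit cost and without a friction-period limit.*

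The reference to recall handling is needed because the TIC-P is given only at T0 to T3 and the article does not say what period each administration covers. Time between windows may have to be extrapolated, and this should be done in the same way for all volumes.

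The cost is one sentence in the economic analysis plan. No extra patients are needed, and the article already intends to estimate losses in these categories. The downside is that societal costs become somewhat higher and more variable, because long absences are no longer cut off. If the authors meant paid work all along, the edit changes nothing in the analysis and removes the risk of misapplication.

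### The ICER and ICUR are defined as effect difference over cost difference, which contradicts the euro-per-QALY ceilings and the below-the-ceiling rule applied to them

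*Protocol article*

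**What the plan says.** All the relevant text is in the Protocol article, Data analysis, Economic evaluation.

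- **Definition of the ICER (base-case analysis):** "the ICER is aimed at dividing the difference in treatment effects of GST and CBT-E by the difference in total costs of both treatments".
- **Definition of the ICUR (same paragraph):** "the difference in QALY gains of both treatments is divided by their respective cost differences".
- **Plane (bootstrap paragraph):** effect difference is on the horizontal axis, and "the vertical axis represents the cost difference between two treatments".
- **Meaning of the ceiling (acceptability-curve paragraph):** "the maximum amount of money that society is willing to pay for one unit of clinical improvement or one unit of QALY gains". The values are EUR 20,000, 50,000 and 80,000 per QALY, "depending the disease burden that will be determined based on the study population".
- **Decision rule:** "If the computed ICER or ICUR for a certain treatment is likely to fall below these thresholds, that treatment is usually considered cost-effective".
- **Acceptability curve:** "the cost-effectiveness acceptability curve will display the probability that the ICER and ICUR of GST fall below a range of existing ceiling ratios", computed from the bootstrap replications.

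**The concern.** The two definitions give effect per euro. The ceilings are euros per unit of effect. The two quantities have reciprocal units and cannot be compared, yet the decision rule and the acceptability curve compare them directly. The inversion is written out separately for the ICER and the ICUR, and nothing elsewhere in the article corrects it.

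Cost-effectiveness is in the title, is a stated hypothesis (Objectives, Economic evaluation), and is meant to inform policymakers and insurers (Implications for healthcare policy and clinical practice). If the definition and the rule were applied together as printed, the analysis could not in practice return a negative answer.

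**Working it through.** The article gives no expected costs, QALYs or standard deviations, so every economic input below is an assumption. Only the ceilings, the definitions and the rule come from the document. Write dE for the effect (QALY) difference and dC for the cost difference, each GST minus CBT-E, and L for the ceiling.

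**Step 1: units.** As written, the ICUR is dE/dC, in QALYs per euro. The ceiling L is in euros per QALY. On a plane with cost on the vertical axis and effect on the horizontal, the slope from the origin is dC/dE, also in euros per QALY. The ceiling and the plane agree with each other, and the definition is the reciprocal of both.

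**Step 2: single scenarios (assumed).** The last column uses net monetary benefit: GST passes if L × dE − dC > 0.

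| dE (QALY) | dC (EUR) | As written, dE/dC | Below 20,000 / 50,000 / 80,000? | Conventional, dC/dE | Net benefit positive at 20,000 / 50,000 / 80,000? |
|---|---|---|---|---|---|
| 0.05 | 500 | 0.0001 | yes / yes / yes | 10,000 | yes / yes / yes |
| 0.05 | 2,000 | 0.000025 | yes / yes / yes | 40,000 | no / yes / yes |
| 0.05 | 5,000 | 0.00001 | yes / yes / yes | 100,000 | no / no / no |
| 0.01 | 5,000 | 0.000002 | yes / yes / yes | 500,000 | no / no / no |
| −0.05 | 5,000 | −0.00001 | yes / yes / yes | −100,000 | no / no / no |

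As written, every scenario passes every ceiling, including the last, where GST is worse and dearer.

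**Step 3: what would make the written ratio fail.** It exceeds 20,000 only if dC is positive and below dE/20,000. For dE = 0.05 that is 0.05/20,000 = EUR 0.0000025. For a full QALY it is 1/20,000 = EUR 0.00005. No realistic cost difference meets this.

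**Step 4: is swapping the ratio enough?** Take independent normal replicates with dE mean 0, SD 0.03, and dC mean EUR 1,500, SD EUR 1,500.

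- Net benefit at L = 20,000 has mean −1,500 and SD √((20,000 × 0.03)² + 1,500²) = √(600² + 1,500²) = 1,615.5. So P(net benefit > 0) = Φ(−1,500/1,615.5) = Φ(−0.928) = 0.177.
- P(GST worse and dearer) = P(dE < 0) × P(dC > 0) = 0.5 × Φ(1) = 0.5 × 0.841 = 0.42. All these replicates have a negative dC/dE, which counts as below the ceiling.

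By simulation, with the below-the-ceiling rule left unchanged for the two ratios:

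| Ceiling (EUR per QALY) | As written, dE/dC | Swapped, dC/dE | Net benefit > 0 |
|---|---|---|---|
| 20,000 | 100% | 58% | 18% |
| 50,000 | 100% | 68% | 24% |
| 80,000 | 100% | 76% | 30% |

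The gap at 20,000 can be accounted for. Replicates that pass wrongly make up 0.45: 0.42 worse and dearer, and 0.03 worse and cheaper with too small a saving. Replicates that fail wrongly make up 0.05: worse and cheaper, but with a saving large enough to pass. This gives 0.176 + 0.450 − 0.050 = 0.576.

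**Step 5: the EDE-Q ICER.** With EDE-Q change as the effect, the conventional ICER is in euros per EDE-Q point. The stated ceilings are per QALY, so they cannot judge it even after the swap.

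**The case against.** The strongest reply is that this is a slip of wording. The plane has the conventional axes, the ceiling is described as money per unit of gain, and the values are quoted per QALY. An experienced health economist would compute cost over effect without noticing the sentence. This largely stands as a statement of intent, and it limits the consequence. A reader might infer that the trial will declare GST cost-effective whatever the data show. The document does not support that, because it would take an analyst who follows the definition literally and ignores the units in the paragraphs that follow. The reply does not remove the contradiction, which is stated twice and corrected nowhere. Nor is it a matter of condensation: the article gives the definition, and gives it wrongly.

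A second reply is that the economic inputs are invented. They are, and the simulated percentages are illustrative only. The result for the ratio as written does not depend on them, since it follows from the mismatch of units (step 3).

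It would also be too general to say that a smaller written ratio always means worse value. That holds when both differences are positive. If GST is better and cheaper, dE/dC is negative, yet that is the best outcome.

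Finally, the primary outcome, sample size, allocation, data collection, costing and bootstrap resampling are untouched. That is correct, and it bears on how much has to change.

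**Conclusion.** The point holds as an internal contradiction. The ICER and ICUR are defined as the reciprocal of the quantity that the ceilings, the decision rule and the plane require. Taken literally, the rule could not return a finding of not cost-effective for any realistic data. The surrounding text makes it likely that the conventional ratio was meant, so this is a wrong definition of a decision quantity to be corrected before analysis, not evidence that the economic conclusion will be wrong.

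Correcting the definition alone leaves a second fault, because the below-the-ceiling rule also passes replicates in which GST is worse and dearer. On the assumed inputs at EUR 20,000, that is the main reason for 58% instead of 18%. The size of this gap depends on the assumed means, SDs and independence. Its cause does not: it arises whenever some replicates have a negative effect difference and a positive cost difference.

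**What to change.** 1. **Definitions (base-case analysis).** ICER = (mean cost GST − mean cost CBT-E) / (mean effect GST − mean effect CBT-E). ICUR = (mean cost GST − mean cost CBT-E) / (mean QALYs GST − mean QALYs CBT-E). State that the EDE-Q effect is signed so that a positive value means improvement.
2. **Acceptability curve.** Define it as the proportion of bootstrap replicates with positive net monetary benefit, L × dE − dC > 0, at each ceiling L, in place of the proportion of ratios below the ceiling.
3. **Ceilings.** Apply the EUR 20,000, 50,000 and 80,000 per QALY ceilings to the ICUR only. Show the EDE-Q result over a range of willingness to pay per EDE-Q point.

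The cost is a few sentences in one section and the matching line of analysis code. The bootstrap replications already planned supply everything needed, with no change to data collection, sample size or design.
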